## Abstract

**Background:**

Fatigue is the most frequent and burdensome symptom of patients with diffuse glioma. It is closely linked to decreased health-related quality of life and symptoms such as depression and sleep disturbances. Currently, there is no evidence-based treatment that targets severe fatigue in patients with brain tumours. Cognitive behavioural therapy is aimed at fatigue-maintaining beliefs and behaviour. This therapy has been proven effective in reducing severe fatigue in cancer survivors and patients with multiple sclerosis. A blended therapy program combines sessions with a therapist with therapist-guided web-based therapy modules. The aim of this randomized controlled trial is to determine the efficacy of blended cognitive behavioural therapy in treating severe fatigue in patients with diffuse glioma.

**Methods:**

We will include a maximum of 100 patients with diffuse glioma with clinically and radiologically stable disease and severe fatigue (i.e. Checklist Individual Strength, subscale fatigue severity ≥ 35). Patients will be randomized to blended cognitive behavioural therapy or a waiting list condition. The 12-week intervention *GRIP on fatigue* consists of five patient-therapist sessions and five to eight individualized web-based therapy modules supported by email contact. The primary outcome measure is fatigue severity. Secondary outcome measures include sleep quality, health-related quality of life, depression, anxiety, functional impairment and subjective and objective cognitive functioning. Primary and secondary outcome measures will be assessed at baseline and after 14 and 24 weeks. Magnetoencephalography and MRI will be used to evaluate potential biomarkers for intervention success. This trial has a Bayesian design: we will conduct multiple interim analyses to test for efficacy or futility of the trial. This is the first trial within the *GRIP trial platform*: a platform developing four to five different interventions for the most common symptoms in patients with diffuse glioma.

**Discussion:**

The results of the *GRIP on fatigue* trial will provide information about the efficacy of this intervention on fatigue in patients with diffuse glioma. Multiple other outcomes and possible predictors of treatment success will also be explored.

**Trial registration:**

Netherlands Trial Register NL8711. Registered on 14 June 2020.

**Supplementary Information:**

The online version contains supplementary material available at 10.1186/s13063-022-06485-5.

## Background

Patients with diffuse glioma are a distinct group within the cancer population, characterized by continuous tumour growth leading to inevitable death. Malignant gliomas are the most common primary brain tumour with an incidence of 6 per 100,000 in Europe [1]. During the disease trajectory, patients experience a multitude of symptoms such as fatigue, cognitive impairment and neurological deficits, resulting in a high symptom burden and impaired health-related quality of life (HRQOL) [2–4].

Fatigue is one of the most frequently reported symptoms in patients with a brain tumour. Cancer-related fatigue (CRF) is “a distressing, persistent, subjective sense of physical, emotional, and/or cognitive tiredness or exhaustion related to cancer that is not proportional to recent activity and interferes with usual functioning” [5]. The prevalence of fatigue in diffuse glioma patients varies between studies; it is reported to affect up to 96% of patients in different stages of the disease [6–10]. In a study of long-term survivors with low-grade glioma, 40% of the survivors reported to be severely fatigued [11]. Additionally in a qualitative study, patients with diffuse glioma described their tiredness as the most severe of the multiple symptoms that they experience [12].

The aetiology of fatigue in patients with a brain tumour is complex and poorly understood. Demographic, biomedical, neuropsychological, psychosocial and behavioural factors may contribute to the origin and persistence of fatigue [13]**.** Fatigue is associated with cognitive complaints and various other symptoms in different symptom clusters, such as depression, anxiety and sleep–wake disturbances, and has a negative influence on role functioning [10]. These different clusters of symptoms have a large impact on everyday life of patients and is linked to a decreased HRQOL [7, 10, 13, 14].

No evidence-based intervention is currently available for the treatment of fatigue in patients with a brain tumour, even though it is thought that effective treatment could improve HRQOL [3, 13]. A 2016 Cochrane review on treating fatigue in primary brain tumour patients could only identify one randomized controlled trial (RCT) that restricted inclusion to severely fatigued patients and had fatigue as the primary outcome measure [8]. This trial was conducted by our group and did not show an effect of the psychostimulant modafinil on fatigue [15]. Inclusion and follow-up rates were lower than expected, because patients were reluctant to take more medication or they experienced side effects. However, several trials that did not limit inclusion to severely fatigued brain tumour patients, but also included brain tumour patients without severe fatigue, have determined positive effects of cognitive rehabilitation and pharmacological treatment on fatigue [16–20]. Despite the lack of evidence-based interventions, the majority of patients seek treatment for their symptoms through complementary medicine [21], indicating a unmet need to alleviate symptoms.

The treatment of CRF has been studied more extensively in non-central nervous system cancer survivors and in palliative cancer patients. Systematic reviews have indicated that Cognitive behavioural therapy (CBT) can reduce fatigue in these patient groups [20, 22]. Fatigue-specific CBT is based on the assumption that cancer treatment and cancer itself can trigger fatigue, but that factors such as sleep disturbances and unhelpful thoughts can contribute to the persistence of fatigue [23, 24]. Treatments targeting such factors may therefore be promising interventions to alleviate fatigue in brain tumour patients. A recent RCT conducted by our group in severely fatigued cancer patients, who were treated with palliative intent, showed a significant reduction of fatigue after a 12-week face-to-face CBT intervention [25]. Cancer survivors who receive CBT for cancer-related fatigue not only report a reduction in fatigue, but also report less cognitive disability and concentration problems [26]. Also, the blended version of the CBT intervention showed a significant reduction of fatigue in breast cancer survivors [27]. CBT as a treatment for fatigue also seems promising in patients with neurological disease. It has shown to be effective in reducing severe fatigue in patients with multiple sclerosis [28] and is studied in treating post-stroke fatigue [29, 30]. Whether fatigued patients with diffuse glioma could benefit from CBT to resolve or reduce fatigue remains to be determined.

The primary objective of this RCT is to determine whether a 12-week therapist-guided blended CBT (BCBT) intervention will reduce severe fatigue post-intervention in patients with diffuse glioma compared to a waiting list condition (WLC). Secondarily, we will determine whether the intervention results in an improvement of sleep quality, HRQOL, depression, anxiety, functional impairment and subjective and objective cognitive functioning. In addition, we will evaluate invested time by patients and therapists and patients’ satisfaction with the treatment and the online platform. Furthermore, we will investigate possible biomarkers for treatment response with exploratory measurements (e.g. advanced neuroimaging and neurophysiology [31–35]).

## Methods

This intervention, the *GRIP on fatigue trial*, is part of the *Guarding Quality of Survivorship (GRIP) trial platform.* The aim of this platform is to develop four to five different interventions for the most common symptoms in patients with diffuse glioma, such as fatigue, cognitive deficits, anxiety and reduced physical fitness [3]. This trial is the first to be launched within this platform. The other trials are under development.

### Recruitment, screening and randomization

Patients visiting the CCA Brain Tumour Center Amsterdam (Amsterdam University Medical Centers)—a tertiary referral centre for patients with brain tumours—will be screened by their treating health care professional (e.g. neurologist, neurosurgeon, psychologist). Patients diagnosed with histologically confirmed diffuse glioma (WHO grade 2, 3 or 4) with clinically and radiologically stable disease and an expected survival of at least three months are eligible for inclusion. A set of laboratory tests is performed: haemoglobin, CRP, sedimentation rate, leukocyte count and differentiation, thrombocyte count, TSH, LDH, ASAT, ALAT, gamma-GT, sodium, potassium, urea, creatinine and glucose. These laboratory results will be screened to exclude medically treatable causes of fatigue.

Patients complete screening questionnaires to check for eligibility: Checklist Individual Strength (CIS) [36] and the Beck Depression Inventory Primary Care (BDI-PC) [37]. See Table 1 for all inclusion and exclusion criteria. The presence of severe fatigue is a criterion for inclusion and is reflected by a score ≥ 35 on the CIS subscale fatigue severity (CIS-fatigue) [36]. The Mini-International Neuropsychiatric Interview-depressive disorder [38] will be conducted over the phone if the patient has a BDI-PC score ≥4. If the criteria of a depression are met, the patient will not be included and will be referred for diagnostics and treatment. Demographic characteristics and disease-related determinants will be collected from the medical file. Comorbidities are assessed by the researcher using the Cumulative Illness Rating Scale [40].

**Table 1 Tab1:** Inclusion and exclusion criteria

Inclusion criteria	Exclusion criteria
(1) Histologically confirmed diffuse glioma WHO grade 2, 3 or 4	(1) Treatable somatic cause that could explain the presence of severe fatigue (other than the underlying disease and its treatment)
(2) Age ≥ 18 years	(2) Primary sleep disorders previously diagnosed by a physician
(3) CIS subscale fatigue severity ≥ 35 (36)	(3) Current treatment by a psychiatrist or psychologist for a psychiatric disorder
(4) Expected survival of at least three months, as determined by treating clinician	(4) Suspected depression by screening with BDI-PC≥4 [37] and The Mini-International Neuropsychiatric Interview depressive disorder [38]
(5) No oncological treatment for at least two months prior to inclusion	(5) Pregnancy or given birth in the past three months
(6) No signs of radiological or clinical tumour progression at the time of inclusion	(6) Pharmacological treatment for fatigue, started in the past three months
(7) Able to speak, read and write Dutch	(7) Karnofsky Performance Status score <70 [39]
(8) Access and ability to use the internet	(8) Corticosteroid use
(9) Written informed consent	

Abbreviations: *CIS* Checklist Individual Strength, *BDI-PC* Beck Depression Inventory – Primary Care

After signing for informed consent and completing the screening procedure, the patient will be randomized to the BCBT intervention or to the WLC group with the use of the web-based computer program, Castor EDC [41]. This program automatically randomizes the patient to one of the two conditions. To keep the number of patients randomized to the two arms balanced throughout the trial, the program uses block randomization with a block size of two and four in random order. A block of two consists of one randomization to the BCGT group and one randomization to the WLC group in random order. A block of four consists of two BCGT randomisations and two WLC group randomisations in random order [42]. After the screening process, the patient is informed on the outcome of the randomization.

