### Sample size calculation and Bayesian design

A multicentre trial by our group on a 12-week BCBT intervention for fatigue among severely fatigued patients with advanced cancer showed that 14 weeks after baseline, patients in the intervention group reported significantly lower CIS-fatigue scores compared to patients receiving care as usual (−7.22, 97.5% CI −12.73 to −1.72; *p*=0.003, Cohen’s *d*=0.72) [25]. Based on these outcomes we anticipated a standardized effect size (Cohen’s *d*) of 0.7 on the CIS-fatigue.

The required number of patients was calculated as 40 per arm. As we expect a maximum of 20% to drop out before the second assessment at 14 weeks after baseline, we aim to recruit a maximum of 100 patients. The trial uses a Bayesian two-arm multistage trial design, where repeated evaluations for efficacy and futility take place after the second assessment CIS-fatigue scores have been observed for 20, 25, 30 and 35 patients in each arm. Frequentist operating characteristics of the trial were evaluated by means of simulation. In the Bayesian model we assumed CIS-fatigue scores to be normally distributed and weakly informative conjugate normal-gamma priors will be used. Parameters for the prior distribution were chosen such that the impact of the prior on the posterior means for the mean and standard deviation for the CIS fatigue scores were negligible. The empirical one-sided significance level was 2.4% and below the desired one-sided significance level of 2.5%. Empirical power was 79% when the standardized effect size was 0.7 (Cohen’s *d*). The expected sample size is 27.4 per arm (54.8 in total) in case of equal means and 31.5 (63 in total) in case standardized effect size is 0.7. A standard two-arm trial without interim analyses would require 43 patients per arm, accounting for 20% drop-out.

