### Statistical analysis

The final analysis is conducted on an intention-to-treat basis. Efficacy of the intervention will be concluded based on the posterior probability as outlined in the previous paragraph. Cohen’s *d* will be calculated as an effect size for CIS-fatigue scores where multiple imputation will be used to deal with missing second measurements. Sensitivity analyses will be performed to assess the robustness of the standardized effect size under different imputation strategies.

In addition, analysis of covariance (ANCOVA) will be performed for the secondary outcomes of the second assessment, with the baseline score on the dependent measure as covariate and group allocation as the fixed factor. A *p*-level of 0.05 will be used. Longer-term follow-up effects will also be tested using ANCOVA, with the baseline score on the dependent measure as covariate. Different tumour types will be added to the model as covariates. Cohen’s *d* will be calculated as effect sizes for the secondary outcomes.

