## Discussion

Fatigue is the most prevalent symptom of brain tumour patients and is linked to several symptoms, such as depression, sleep disturbances, anxiety, and decreased HRQOL. Patients with diffuse glioma have poor survival and high symptom burden, so the quality of survivorship should be an important factor of treatment. A significant part of care for quality of survivorship is symptom management [63]. Cognitive behavioural interventions seem promising in reducing fatigue severity based on their effectiveness in cancer survivors and palliative cancer patients.

One of the challenges in brain tumour research is the low rate of patient inclusion. Multiple provider reported barriers could explain these low rates, including concerns about the costs and time for patients, frequent hospital visits, suboptimal discussion of possibilities of trial participation and barriers in completing follow-up [64, 65]. This trial tackles some of these barriers by using a blended care intervention with telemedicine limiting visits and travel time. The recruiting clinicians are part of the research team, ensuring a good workflow for patients and clinicians. A researcher will coordinate recruitment, limiting the time spent on recruitment by clinicians. Also, by randomizing patients to a WLC group in the trial, we overcome a potential barrier for patients in enrolling in a trial compared to trials with a care as usual control group. If recruitment is slower than expected after a year, we will include more hospitals for recruitment.

Furthermore, this trial incorporates a Bayesian trial design with a flexible number of patients to be included, ensuring that only the number of patients actually needed to show relevant results will be included. Our trial will include patients with different types of diffuse glioma. This can result in different survival rates, rates of tumour recurrence and dropouts. Subgroup analyses per tumour type may help to explore potentially varying treatment effects.

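### The primary Bayesian comparison states no tumour covariate and randomisation balances only arm totals, so an early stop at 20 patients per arm can rest on an unequal tumour mix

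*Protocol article*

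**What the plan says.** **Allocation** (Recruitment, screening and randomization). The stated aim is balance in numbers: "To keep the number of patients randomized to the two arms balanced throughout the trial, the program uses block randomization". The section gives the block sizes and the make-up of each block, and names no stratum. Entry is open to WHO grades 2, 3 and 4.

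**Primary decision** (Sample size calculation and Bayesian design; Termination for efficacy or futility). CIS-fatigue at 14 weeks is modelled as normal with conjugate normal-gamma priors. Efficacy needs a posterior probability above 99% that the intervention mean is the lower one. Futility is a predictive probability of success below 10%. Looks take place once week-14 scores "have been observed for 20, 25, 30 and 35 patients in each arm", and the maximum is fixed as follows: "The required number of patients was calculated as 40 per arm". No covariate is mentioned for this comparison.

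**Tumour type elsewhere.** In Statistical analysis, the paragraph on the secondary and longer-term ANCOVAs says: "Different tumour types will be added to the model as covariates". The Discussion says of enrolling different glioma types: "This can result in different survival rates, rates of tumour recurrence and dropouts".

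**The concern.** The protocol regards tumour type as relevant to outcome and adjusts the ANCOVAs for it. The one comparison that can stop the trial has no such protection, either in the allocation or in its stated model. Blocks of two and four on a single list equalise arm sizes but leave tumour mix to chance. Chance matters most in small samples, and this design can end at 20 observed patients per arm.

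An efficacy claim made at that look with visibly unequal tumour mix would be open to challenge. If tumour grade predicts fatigue, precision that the collected data could supply is also left unused.

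**Working it through.** **1. The plan's own figures.** Inputs from the article: looks at 20, 25, 30, 35 and 40 observed per arm, the 99% and 10% thresholds, d = 0.7 and 20% drop-out. A simulation of 20,000 trials per scenario with a near-flat prior gave:

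| | Stated | Simulated |
|---|---|---|
| One-sided alpha | 2.4% | 2.34% |
| Power at d = 0.7 | 79% | 78.7% |
| Expected n per arm, no effect | 27.4 | 21.97/0.8 = 27.5 |
| Expected n per arm, d = 0.7 | 31.5 | 25.61/0.8 = 32.0 |

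The design is reproduced closely if the stated expected sizes include drop-out.

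**2. How often the trial ends at the first look.** The article gives no figure. The simulation gives 78% under no effect, 42.5% at d = 0.5 and 50% at d = 0.7. A known-variance check at 20 per arm:
- Efficacy if z > 2.326. Futility if z < (2.326 − 1.282)/√2 = 0.739.
- With d = 0: 0.010 + 0.770 = 0.78.
- With d = 0.7, mean z = 0.7 × √10 = 2.21: 0.455 + 0.070 = 0.525.

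If the stated expected sizes were observed counts without drop-out inflation, the first-look share could be at most (40 − 27.4)/20 = 63% under no effect and (40 − 31.5)/20 = 42.5% at d = 0.7.

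**3. Imbalance in grade-4 share.** The grade mix is not given, so p = 20%, 30% and 40% are assumed. The SD of the difference in share is √(2p(1 − p)/n).

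| p | SD, n = 20 | P(gap ≥ 20 points), n = 20 | P(gap ≥ 20 points), n = 40 |
|---|---|---|---|
| 20% | 12.6 points | 16% | 4% |
| 30% | 14.5 points | 23% | 7% |
| 40% | 15.5 points | 26% | 9% |

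**4. What a gap does to the estimate.** The article gives no effect of grade on CIS-fatigue, so g = 0.25 to 0.8 SD is assumed.
- Shift = g × 0.20 = 0.05 to 0.16 SD, or 7% to 23% of 0.7.
- The standard error at 20 per arm is √(2/20) = 0.316 SD, so z moves by 0.16 to 0.51.

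First-look efficacy rates with a 40% share (300,000 simulated trials per setting):

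| g | True d | All allocations | Gap ≥ 20 points, favourable | Gap ≥ 20 points, unfavourable |
|---|---|---|---|---|
| 0.5 | 0 | 1.0% | 2.4% | 0.3% |
| 0.8 | 0 | 1.0% | 3.4% | 0.1% |
| 0.5 | 0.7 | 42% | 57% | 28% |
| 0.8 | 0.7 | 42% | 66% | 21% |

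The average rate is kept. The result of one trial depends strongly on its own imbalance.

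**5. What the covariate gains.** With total SD 1 and a 30% share, residual variance after adjustment is 1 − 0.3 × 0.7 × g² = 1 − 0.21g². Approximating the design by one test at 40 per arm, power = Φ(0.7√20/√(1 − 0.21g²) − 2.326):
- No adjustment: Φ(3.130 − 2.326) = 78.9%.
- g = 0.25: residual variance 0.987, power 79.5%.
- g = 0.5: residual variance 0.948, power 81.3%.
- g = 0.8: residual variance 0.866, power 85.1%.

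Simulating the full sequential design gives about 80%, 81% and 85%. If grade has no effect, less than 1 point is lost.

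**6. What stratification adds.** In a separate simulation (60,000 trials per setting, 30% share):

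| | g = 0.5 | g = 0.8 |
|---|---|---|
| As planned | 79.1% | 79.2% |
| Stratified, not adjusted | 79.8% | 80.8% |
| Adjusted, not stratified | 80.6% | 84.1% |
| Both | 81.4% | 84.8% |

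Stratification adds 0.8 and 0.7 points beyond adjustment. Stratified data analysed without the term gave type I error of 1.5-2.0%.

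**The case against.** The strongest reply is that chance imbalance under valid randomisation is already part of the sampling variance. A shift of 0.10-0.16 SD (g = 0.5-0.8) is a third to a half of one standard error at the first look, and it falls in either direction. The stated 2.4% and 79% are met within simulation error without stratification. All of this stands. A reader might infer that the unstratified allocation biases the trial or inflates false positives. It does not: the raised rates appear only after conditioning on a favourable gap.

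Two further readings go beyond the article. One is that the protocol names grade as what drives survival, recurrence and drop-out. It speaks of tumour types, says only that such differences can result, and links neither type nor grade to CIS-fatigue. Grade is a proxy chosen here because histology is an entry criterion. The other is that most trials end at the first look. That is clear only under no effect. At d = 0.7 it is about half, and at d = 0.5 a minority.

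The drop-out route is weak. A 20-point gap is four patients at 20 per arm. If drop-out differed by 20 points between grades (assumption), that is 0.8 of a patient. Patients who leave are still asked to complete the assessments, and multiple imputation with sensitivity analyses is planned for the effect size.

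An unseen analysis plan may add a tumour term. The article, however, commits to a conjugate model and a comparison of arm means, and it mentions tumour type only in the ANCOVA paragraph. The mismatch is in what it states.

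**Conclusion.** The point holds as a modest, inexpensive improvement, not as an error that invalidates the design. The comparison that can stop the trial lacks the tumour adjustment given to the ANCOVAs, and the allocation does not make up for it. At 20 observed per arm, a grade-4 gap of 20 points or more is expected in about 16-26% of trials, for an assumed share of 20-40%. The cost is lost precision and a less credible single early result. Adjustment would raise power from about 79% to about 80-85%, assuming a 30% share and a grade effect of 0.25-0.8 SD. The lower end of that effect range makes the gain small. The documents do not support the view that stratification is required, since nearly all of the gain comes from the model term.

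**What to change.** **Main change.** Add one prespecified tumour term to the primary Bayesian model at every interim look and at the final analysis: WHO grade 4 versus 2-3, or the tumour type already used in the ANCOVAs. Repeat the simulation of type I error, power and expected sample size with that model. Fix the term before any comparative look. At submission twelve patients were enrolled, against the 40 observed that the first look needs.

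**Cost.** The conjugate two-mean model becomes a normal linear model, and the efficacy and predictive probabilities must be recomputed from it. The simulation must be repeated. Less than 1 point of power is lost if grade has no effect. No extra patients or data are needed.

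**Optional.** Stratify the remaining allocations by the same factor in the existing web system. For 40 patients in two groups, this cuts the chance of a gap of 10 points or more from 59-63% to about 0.4% before drop-out. It needs an amendment and a new allocation list, leaves patients already enrolled unstratified and may leave one more incomplete block. It should be done only together with the model term, because an unadjusted analysis of stratified data is conservative.
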